## Data collection and management

### Plans for assessment and collection of outcomes {18a}

#### Collection of outcomes

In total, participants will undergo three in-person neuropsychological assessments at baseline, post-test, and 3-month FU (Fig. 2). An overview of all assessments is presented in Table 2. All assessments are conducted in German by experienced research fellows or trained medicine or psychology student assistants. In general, demographic and clinical data (e.g., age, sex, PD duration, concomitant diseases, possible DBS surgery) as well as cognitive reserve measured by the Lifetime of Experiences Questionnaire (LEQ) [72, 73] are collected at baseline only. To control for stable medication treatment, all medication is listed and documented at the beginning of each assessment. This is followed by the neuropsychological assessment. An elaborate test battery with established psychometric instruments was set up to cover cognitive, motor, and further (neuro)psychological outcomes, which may be related to a CT effect. Regarding cognition, at least two tests per cognitive domain are used to allow a level 2 diagnosis of PD-MCI and the exclusion of PDD [103]. Additionally, participants undergo a short motor examination to assess motor outcomes (e.g., severity of motor symptoms, dual-task performance). Short breaks are administered during the assessment as needed. At the end of each neuropsychological assessment, several self-rating questionnaires are handed out to participants to fill out at home and return in a provided pre-addressed, stamped envelope. To assess CT feasibility and acceptability, participants of the EG receive a pen-and-paper CT diary at the end of their baseline neuropsychological assessment. Additionally, technical CT data will be used to assess CT feasibility. The following sections provide an overview of all outcome measures.

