### Participant timeline {13}

Interested individuals undergo a brief telephone screening, in which they receive information on the study purposes and an initial screening for the inclusion criteria. Those meeting the inclusion criteria are invited for baseline assessment, either at the research facility, a room leased specifically for the purpose of the assessment, their home, or a room at a supporting research facility. Figure 2 shows the study design. At baseline assessment, participants first receive detailed written information on the study and are instructed to pose any remaining questions to a trained examiner before providing written informed consent (see Sect. “Who will take informed consent? {26a}”). Following consent, all inclusion criteria are assessed in detail via a checklist. To ensure the exclusion of dementia and severe depressive symptoms, the MoCA and BDI-II are administered, respectively, and scored by the trained examiner before further assessments are undertaken. If inclusion criteria are not met, the assessment is not continued. Eligible participants continue to baseline assessment and, upon completion, are randomized to either the EG or CG (see Sect. “Sequence generation {16a}”). At the end of the baseline assessment, members of the EG receive their printed CT access data, program details (i.e., CT checklist, step-by-step CT guide, and brief CT diary), and a handout with information on the voluntary biweekly video-based consultations either in person or via post to their home by an unblinded member of the study team (author [name]). Additionally, an email is sent to all participants of the EG containing a link with access to the psychoeducational videos, so they can successfully participate in the CT and watch the videos from home. In contrast, those in the CG do not receive any information on the CT but instead are instructed in person, via telephone, or via email by the same unblinded team member (author [name]) to continue their care as usual until the next appointment is agreed upon. According to group allocation, a 5-week CT period (EG) or care as usual (CG) follows, concluding with a post-test at week 7 and a 3-month FU assessment at week 19. These latter assessments are again conducted at a research facility, the participants’ home, or a room leased for the occasion by a blinded examiner.

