### Concealment mechanism {16b}

Allocation lists are securely stored on a password-protected computer drive. Allocation is performed by one of two unblinded supervisory team members (authors [name], [name]), who both have access to the lists but are not involved in neuropsychological assessment. Group allocation is only revealed to participants at the end of their baseline assessment.

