### Implementation {16c}

Blinded research fellows and/or trained medicine and psychology student assistants enroll participants and conduct neuropsychological assessments throughout the study. At the end of each baseline assessment and in the absence of the respective examiner, one research fellow (author [name]) receives information on group allocation from one of the supervisory members (authors [name], [name]) and subsequently informs participants about their group allocation. From this point forward, this research fellow (author [name]) is unblinded to all group allocations, and hence does not conduct any post-test or FU assessments, but handles all tasks related to group knowledge, i.e., CT set-up, monitoring of CT progress, leading the video-based consultations, overseeing study progress, and responding to inquiries to the study-specific email. All other examiners remain blinded through assessments and data management.

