## Assignment of interventions: blinding

### Who will be blinded {17a}

During baseline assessments, both examiners and participants are blinded. Randomization and group allocation are carried out following baseline assessment by unblinded team members (see Sects. “Concealment mechanism {16b}” and “Implementation {16c}”). Further assessments (post-test and FU) will be carried out single-blinded, i.e., all examiners will be blind to group allocation, while participants are aware of their group. To ensure examiner blinding throughout post-test and FU assessments, participants are reminded prior to every assessment not to give hints on their group allocation. Besides blinded neuropsychological assessments, data management (e.g., data entry, data monitoring) is also carried out in a blinded manner, i.e., all paper-based and digitalized assessment data are pseudonymized and without any information on group allocation (see Sects. “Data management {19}” and “Confidentiality {27}”); therefore, all research fellows and student assistants remain blinded.

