## Statistical methods

### Statistical methods for primary and secondary outcomes {20a}

The primary analysis is according to the intention to treat, with no exclusions. The change from baseline in the primary outcome MoCA is analyzed by a linear mixed model for repeated measures (MMRM) with fixed effects for baseline, group, time, and group × time interaction (ARH1-structured variance–covariance matrix over time). The primary comparison at T1 (week 9) is based on a pairwise contrast of estimated marginal means with a 95% confidence interval. Secondary outcomes (i.e., further timepoints and measures) are analyzed along the same line, however from an exploratory viewpoint only; thus, no multiplicity adjustment is required. Where available, observed changes will also be interpreted in relation to published minimally clinically important differences (MCIDs) to evaluate clinical relevance in addition to statistical significance.

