### Methods for additional analyses (e.g., subgroup analyses) {20b}

Predictiveness of change in the main outcome and secondary outcomes regarding baseline, age, sex, education, disease-related factors (e.g., severity of motor symptoms), and (neuro)psychological factors (e.g., cognitive baseline level, self-efficacy, and depressive symptoms) is explored by adding both main effects and interactions with group to the model equation. Moreover, models are fitted in corresponding subgroups.

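### The protocol does not ensure that the take-home baseline questionnaires are completed before participants learn their group

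*Protocol article*

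**What the plan says.** **Questionnaires.** Collection of outcomes: "At the end of each neuropsychological assessment, several self-rating questionnaires are handed out to participants to fill out at home". They come back by post. The rule applies to every assessment, so to baseline as well. The text does not list which instruments go home, and Table 2 cannot be seen in the version at hand.

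**Randomisation and disclosure.** Participant timeline {13}: "Eligible participants continue to baseline assessment and, upon completion, are randomized to either the EG or CG". Concealment mechanism {16b}: "Group allocation is only revealed to participants at the end of their baseline assessment". Implementation {16c}: one unblinded research fellow learns the allocation at the end of the baseline assessment and "subsequently informs participants about their group allocation".

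**Materials.** Participant timeline {13}: "At the end of the baseline assessment, members of the EG receive their printed CT access data, program details". Delivery is in person or by post, and the video link goes out by email. Control participants are told in person, by telephone or by email to carry on with usual care.

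**Blinding.** Who will be blinded {17a}: "During baseline assessments, both examiners and participants are blinded".

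**Analysis.** Section {20a} models change from baseline in the MoCA and also carries baseline as a covariate. For the rest, "Secondary outcomes (i.e., further timepoints and measures) are analyzed along the same line", as exploratory analyses. Section {20b} lists candidate predictors, including "cognitive baseline level, self-efficacy, and depressive symptoms", each entered as a main effect and as an interaction with group.

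**The concern.** The baseline questionnaires leave with the participant at the point where the participant is, or is about to be, told the group. A form filled in at home afterwards records how someone rates themselves knowing that they will train now or wait. Such a value is measured after allocation and can respond to it.

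The planned model relies on it twice, once when it is subtracted and once when it is adjusted for. Both uses assume that baseline cannot depend on group. If it does, the group contrast for the take-home outcomes is shifted. A self-efficacy score recorded after disclosure may also mix the participant's prior level with a reaction to the allocation, so its interaction with group would not be a clean test of effect modification. The objectives name both improvement in noncognitive functions and predictors of responsiveness, so these results will be read.

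**Working it through.** **Step 1: order of events.** Putting the sections side by side gives:

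1. Consent, eligibility check, MoCA and BDI-II, both scored before anything further ({13}).
2. Rest of the in-person baseline assessment.
3. End of the visit: questionnaires handed out for home completion (Collection of outcomes). The same section has EG participants receive the training diary at this point.
4. Also at the end of the visit: randomisation and disclosure, with training access given in person or sent by post ({13}, {16b}, {16c}).
5. At home: questionnaires filled in and posted.

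No section makes completion or return of the forms a condition for step 4. An EG participant can leave with a training diary and blank baseline forms. A participant told later by telephone, email or post may have completed the forms first. Either order is compatible with the text.

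**Step 2: what a shifted baseline does.** The plan has no figure to reproduce here. The following is an illustration; δ and ρ are assumptions, since the document gives neither. Work in SD units:

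- x₀: score before disclosure; G: 1 for EG, 0 for control
- recorded baseline x = x₀ + δG
- post-test y = ρx₀ + τG + error, where τ is the true effect

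Substituting x₀ = x − δG gives y − x = (ρ − 1)x + (τ − ρδ)G + error. The group coefficient is therefore off by −ρδ if the shift has gone by post-test. If the same shift is still present in y, δ is added and the error becomes (1 − ρ)δ. If the questionnaire's own baseline is left out of the model, the error is 0 in the first case and δ in the second.

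| δ | ρ | planned model, shift gone | planned model, shift persists | own baseline omitted, gone / persists |
|---|---|---|---|---|
| 0.1 | 0.5 | −0.05 | +0.05 | 0 / +0.10 |
| 0.1 | 0.8 | −0.08 | +0.02 | 0 / +0.10 |
| 0.2 | 0.7 | −0.14 | +0.06 | 0 / +0.20 |
| 0.3 | 0.5 | −0.15 | +0.15 | 0 / +0.30 |
| 0.3 | 0.8 | −0.24 | +0.06 | 0 / +0.30 |

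All signs reverse if knowing the group makes EG ratings worse rather than better.

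**Step 3: check by simulation.** With 200,000 simulated participants, τ = 0.30 (chosen only for illustration), ρ = 0.7, δ = 0.2 and the shift gone at post-test, the planned model returned 0.16, matching 0.30 − 0.7 × 0.2 = 0.16. With the pre-disclosure baseline it returned 0.30.

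**Step 4: cost of leaving out the baseline.** At ρ = 0.7 the residual variance is 1 − 0.7² = 0.51 with the baseline and 1.00 without it. The ratio is 1/0.51 = 1.96, so the standard error grows by about √1.96 = 1.40, before any recovery through other covariates.

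**The case against.** A reader might infer more than the document supports, in five ways.

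- **That every baseline form was completed after disclosure.** The text does not fix that order. Telephone, email and postal contact leave room for forms completed while still blind. What stands is that nothing ensures it.
- **That the blinding statement is contradicted.** Collection of outcomes describes three in-person assessments, with the forms handed out when each ends. If baseline assessment means the visit, {17a} is true as worded and merely silent on the home forms.
- **That all patient-reported outcomes are affected.** The BDI-II is done on site before allocation, so being a questionnaire does not make an instrument take-home. That the self-efficacy scale goes home is a strong inference from its being self-rated, not a stated fact.
- **That the bias can be set against the effect size used for planning.** The d of 0.3–0.5 in Sample size {14} refers to global cognition, which is unaffected. No effect size is planned for the questionnaires.
- **That the planned model should be replaced.** Participants know their group at post-test and follow-up too, so an expectancy shift may persist. In that case, at δ = 0.2 and ρ = 0.7, the planned model is off by 0.06 SD and a model without the own baseline by 0.20 SD.

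It is also fair that the affected analyses are exploratory and no confirmatory conclusion depends on them. Being exploratory removes the need for multiplicity adjustment; it does not turn a value recorded after disclosure into a baseline.

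**Conclusion.** The point holds as a gap in the procedure: the baseline of the take-home questionnaires is not secured against knowledge of the allocation, while {20a} and {20b} treat it as if it were. For many participants it may be unblinded; how many cannot be told from the document.

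Under the assumed ranges (δ 0.1 to 0.3 SD, ρ 0.5 to 0.8), the error of the planned model lies between −0.05 and −0.24 SD if the shift is gone at post-test, and between +0.02 and +0.15 SD if it persists. These figures show only that the matter need not be negligible. They are not estimates for this trial, whose direction and size remain unknown.

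The primary comparison on the MoCA, the baseline BDI-II and the examiner-administered tests are not touched. The consequence is confined to exploratory analyses of the take-home outcomes and, if the scale is among them, of self-efficacy as a predictor.

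**What to change.** **Participants still to be enrolled.** Release the allocation only after the baseline questionnaires have been completed at the visit or received back. This costs a short delay. Trial status gives protocol version 6.0 as 26 November 2025 and expects recruitment to end with 2025, so the change may reach few people.

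**Participants already enrolled.**

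- Compare completion or return dates, where they exist, with the date of disclosure, and report by arm how many forms came first. A return date only bounds the completion date.
- Keep the planned model for the take-home outcomes. Add a sensitivity analysis that adjusts only for covariates measured before allocation (MoCA, BDI-II, age), or one restricted to forms completed before disclosure. Both lose precision. The restricted set also needs a check of balance, because the routes of disclosure differ between arms.
- Read the two analyses together. Neither is free of bias if expectancy persists at post-test.
- Label self-efficacy recorded after disclosure as such, and do not present its interaction with group as a clean baseline modifier.

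**Text.** Limit the statement in {17a} to the in-person baseline assessment, and say which instruments go home and when they are due relative to disclosure. This costs a sentence or two.

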### Primary outcome

The primary outcome measure is the German version of the MoCA [56], a screening tool to detect MCI. The MoCA is a widely recommended screening tool for cognition in clinical trials [104]. The final score ranges from 0 to 30 points, with higher scores indicating better cognitive performance. Scores < 21 indicate PDD, scores from 21 to 25 indicate PD-MCI, and scores ≥ 26 indicate age-appropriate cognitive performance [60]. The MoCA has high sensitivity (90%) and specificity (87%) for detecting MCI [56, 60, 105] and has good reliability (Cronbach’s alpha of 0.83 [56]) and validity (receiver operating characteristics area under the curve 0.87 [106]).

### Secondary outcomes

#### Secondary cognitive outcomes

Regarding secondary cognitive outcomes, the extended version of the Consortium to Establish a Registry for Alzheimer’s Disease (CERAD-Plus) [74–76] is the basis of the neuropsychological assessments. This test battery is complemented by additional cognitive outcomes according to the LANDSCAPE study [107] to give at least two outcome measures per cognitive domain (Table 2). A second measure of global cognition is the Mini-Mental Status Test (MMST) involved in the CERAD-Plus test battery. Executive functions (i.e., semantic and phonemic fluency, cognitive flexibility, and logical thinking) are assessed using the CERAD-Plus animal and s-words, CERAD-Plus Trail Making Test (TMT) versions A and B, and the German performance test system (Leistungsprüfsystem 50+ [LPS 50+]) subtest 4 [77], respectively. Working memory and attention are assessed using the Wechsler Memory Scale—Revised (WMS-R) digit span forward and backward [78] as well as the Brief Test of Attention (BTA) [79]. Visuocognition, i.e., construction and visual perception, is measured using the CERAD-Plus figure copying, the Benton Judgement of Line Orientation (BJLO) [80, 81], and the LPS 50+ subtest 9, respectively. Verbal memory is measured using the CERAD-Plus wordlist learning, recall, and recognition subtests, while visuospatial memory is assessed using the CERAD-Plus figure recall subtest. Language, specifically naming and language comprehension, is assessed using the CERAD-Plus Boston Naming Test (BNT) and the Aphasia Checklist (ACL) auditory language comprehension subtest [82], respectively. Lastly, subjective cognitive impairment is assessed using the Multiple Domain Subjective Cognitive Decline Evaluation (Multi-SubCoDE), which has not been published but has been used previously [83, 84].

#### Secondary motor outcomes

Secondary motor outcomes include the assessment of motor function and the level of severity of motor impairment as assessed by the Movement Disorder Society’s Unified Parkinson’s Disease Rating Scale part III (MDS-UPDRS-III) [85] and Hoehn & Yahr stage [85], respectively. Assessment of the MDS-UPDRS-III is video recorded for each participant during the assessments and scored at a later time point by a blinded member of the study team. Dual-task performance is measured using the Timed Up and Go (TUG) test [86, 87] consisting of three subtests: the standard variation, the manual task, and the cognitive task. Additionally, freezing of gait and physical activity are assessed using the Freezing of Gait Questionnaire (FOG-Q) [88, 89] and the Physical Activity Scale for the Elderly (PASE) [90], respectively.

#### Secondary neuropsychiatric outcomes

Regarding neuropsychiatric outcomes, depressive symptoms are assessed according to the BDI-II [61], apathy according to the Apathy Evaluation Scale (AES) [91, 92], fear of progression according to the short version of the fear of progression questionnaire (Progredienzangst-Fragebogen Kurzform [PA-F-KF]) [93], and fear of falling according to the Falls Efficacy Scale (FES) [94, 95].

#### Secondary outcomes: sleep/fatigue

Sleep is evaluated using the Parkinson’s Disease Sleep Scale (PDSS) [96] and fatigue is assessed according to the Fatigue Scale for Motor and Cognitive Functions (FSMC) [97].

#### Secondary outcomes: further non-motor outcomes

Lastly, several other non-motor outcomes are examined, i.e., health-related QoL, self-efficacy, ADL, and non-motor symptoms, using the Parkinson’s Disease Questionnaire (PDQ-39) [98, 99], the Self-Efficacy Scale (Selbstwirksamkeitserwartung [SWE]) [100], the Bayer Activities of Daily Living Scale (B-ADL) [101] and the Non-Motor Symptoms Questionnaire (NMSQ) [102], respectively.

#### CT feasibility and acceptability outcomes

Feasibility of the digital CT is assessed in terms of participants’ ability to complete the intervention as prescribed. Indicators include CT dropout rate, number of training days completed, total duration of training, and technical handling, including any problems encountered during CT intervention. These data are collected from the CT software and via a pen-and-paper CT diary distributed to participants of the EG after their baseline assessment. Based on current literature, the CT intervention is considered feasible if CT dropouts are ≤ 14% [43] and participants completed at least 80% (i.e., ≥ 16/20) of the training days and the total training duration (i.e., ≥ 720/900 min) [30, 84]. Via optional free-text comments in the CT diary, participants can give qualitative feedback on technical handling of the CT (cf. next paragraph).

CT acceptability is evaluated based on participants’ experience with the CT. In the pen-and-paper CT diary, daily ratings capture the motivation to engage in CT on a 5-point scale (0 = “not motivated at all,” 5 = “highly motivated”) and satisfaction with each session (0 = “not good at all,” 5 = “very good”). Weekly ratings assess how well participants were able to integrate CT into their daily routines and the extent to which external factors, such as tiredness or stress, impacted training (0 = “not at all,” 5 = “very much”). At the end of the CT intervention, participants provide an overall evaluation using the German grading system (1 = “very good,” 6 = “unsatisfactory”) and indicate if they would recommend the CT (“yes”/“no”). Optional free-text comments are collected after each session, weekly, and in the final evaluation to capture qualitative feedback. The intervention is considered acceptable if the average scores across CT sessions and weekly ratings are ≥ 4/5 points and the overall evaluation reaches a score of ≥ 3.5/6 points according to the German grading system. Additionally, if more than 80% of participants recommend the CT, it will be considered acceptable. If the criteria for feasibility and acceptability are not met, the results of the CT efficacy should be interpreted cautiously as the intervention may not have been delivered effectively.

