### Objectives {7}

Based on a hybrid type 1 clinical trial design [54], this study has three objectives. The first is to assess the short- and long-term effects of a 5-week digital CT intervention (“HeadApp/NEUROvitalis Digital” [55]) in people with advanced PD on global cognitive functions, with the Montréal Cognitive Assessment (MoCA) [56] as the primary outcome, and other cognitive, motor, and (neuro)psychological variables as secondary outcomes (e.g., specific cognitive functions, depressive symptoms, and severity of motor symptoms). It is expected that CT will improve global cognition and other cognitive and noncognitive functions, both in the short term and over a 3-month follow-up period. The second objective is to examine the feasibility and acceptability of the CT. Specifically, it is hypothesized that the CT intervention is feasible in terms of adherence to the training schedule, completion of training days, and technical handling and is acceptable in terms of participant motivation, satisfaction, and integration of CT into daily life. Finally, the study seeks to explore and identify possible predictors of CT responsiveness, including sociodemographic factors (e.g., age, sex, education), motor (e.g., severity of motor symptoms), and cognitive and (neuro)psychological factors (e.g., cognitive baseline level, self-efficacy, and depressive symptoms).

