### Intervention description {11a}

#### Experimental group

Participants engage in a 5-week training schedule using the scientifically based and standardized CT “HeadApp/NEUROvitalis Digital” [55], a class 1 medical device for the prevention and therapy of cognitive dysfunctions. The CT “HeadApp/NEUROvitalis Digital” is based on the pen-and-paper NEUROvitalis program [64], an evidence-based multidomain intervention developed for cognitive rehabilitation in older adults and neurological populations (e.g., PD). The analogue NEUROvitalis program has demonstrated efficacy and high user acceptance in several RCTs, including people with PD [65–67]. The digital version used in this study preserves the structure and cognitive-domain coverage of the original program while allowing home-based, adaptive training and automated performance tracking. Participants can access CT remotely and free of charge during study participation. For each participant, CT is supervised by a single member of the study team (author [name]).

Although the CT was conceptualized without specifically targeting PD, a CT schedule considering the specific cognitive profile of people with PD was developed for this study (i.e., structured rather than unstructured CT incorporating PD-relevant domains, such as working memory, memory, and executive functions [65, 66, 68]). Specifically, the structured CT schedule consists of five working memory exercises and five exercises targeting various cognitive functions: episodic memory, executive function, attention, visuocognition, and language (Fig. 1). It was specifically designed for this study and implemented into the CT program, maintaining a balanced and fixed order of exercises throughout, which participants and the study team cannot alter during the study (Table 1). The schedule consists of 20 training days to be completed over the 5-week training period. Participants are instructed to train four times per week (i.e., 4 days) for 45 min per training day, equaling 900 min in total. A training day consists of a set of three successive exercises targeting different cognitive domains (15 min each) in a prescribed order. Training frequency and duration are in accordance with previous studies on CT in PD [65, 68].

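### The external-factors rating, which is unfavourable when high, counts toward the 4/5 acceptability criterion without reversal or exclusion

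*Protocol article*

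**What the plan says.** The section on CT feasibility and acceptability outcomes in the protocol article describes four repeated diary ratings, each anchored at 0 and 5.

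- Motivation, rated daily: "daily ratings capture the motivation to engage in CT on a 5-point scale (0 = “not motivated at all,” 5 = “highly motivated". High is favourable.
- Satisfaction, rated daily: "satisfaction with each session (0 = “not good at all,” 5 = “very good". High is favourable.
- Integration, rated weekly: "Weekly ratings assess how well participants were able to integrate CT into their daily routines". High is favourable.
- External factors, rated weekly: "the extent to which external factors, such as tiredness or stress, impacted training (0 = “not at all,” 5 = “very much". High is unfavourable.

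The decision rule follows in the same section: "The intervention is considered acceptable if the average scores across CT sessions and weekly ratings are ≥ 4/5 points". It adds a condition on the overall grade and then a recommendation clause: "Additionally, if more than 80% of participants recommend the CT, it will be considered acceptable". If the feasibility and acceptability criteria are missed, the section asks for caution in reading the efficacy results.

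The Objectives section {7} states the hypothesis more narrowly. The training is expected to be "acceptable in terms of participant motivation, satisfaction, and integration of CT into daily life". External factors are not named there.

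**The concern.** The rule applies one threshold to the weekly ratings as a group, but the two weekly ratings point in opposite directions. Taken literally, a participant whose training was undisturbed lowers the diary score, and one whose training suffered from fatigue or stress raises it. The rule also counts an item that lies outside the construct in the Objectives.

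The diary component could therefore err in both directions. It could fail a training that went smoothly, or pass one whose favourable ratings fall short of 4. Acceptability is part of the trial's second objective. The Discussion makes its case for bringing digital training into daily life conditional on feasibility and acceptability, and a missed criterion changes how the efficacy result is to be read. The Discussion also expects symptom fluctuations that may affect training in this population, so the external-factors ratings can be expected to vary.

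**Working it through.** The 4/5 cut-off is set by rule and not derived from other figures, so there is nothing to reproduce. The check is to apply the rule as written.

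**Inputs.** The cut-off of 4 and the item directions come from the acceptability section. The number of ratings comes from the intervention description: "The schedule consists of 20 training days to be completed over the 5-week training period". A participant who completes everything, with one answer per item per day or week, gives 20 × 2 = 40 daily and 5 × 2 = 10 weekly ratings, 50 in all. Let q be the common mean of the three favourable items and x the mean external impact. The values of q and x below are assumptions for illustration.

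**Formulas.** The article does not say which average is meant, so four forms are tried:

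- each item separately: the external item needs x ≥ 4
- the two weekly items together: (q + x)/2
- the four item means, equally weighted: (3q + x)/4
- all ratings pooled: (45q + 5x)/50

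**Results at q = 4.3**, where the favourable items alone would pass:

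| Form of average | x = 1 | x = 4 | Change per point of x |
|---|---|---|---|
| External item alone | 1, fail | 4, pass | 1.00 |
| Two weekly items | (4.3 + 1)/2 = 2.65, fail | (4.3 + 4)/2 = 4.15, pass | 0.50 |
| Four item means | (12.9 + 1)/4 = 3.475, fail | (12.9 + 4)/4 = 4.225, pass | 0.25 |
| 50 ratings pooled | (193.5 + 5)/50 = 3.97, fail | (193.5 + 20)/50 = 4.27, pass | 0.10 |

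Whenever the item is included, the sign is wrong. The weekly mean at q = 4.3 needs x ≥ 2 × 4 − 4.3 = 3.7.

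**How far the pooled result can move.** Setting (45q + 5x)/50 = 4 gives q = (200 − 5x)/45. This is 200/45 = 4.44 at x = 0, 195/45 = 4.33 at x = 1, and 175/45 = 3.89 at x = 5. Under pooling, the item can therefore decide the result only when the favourable ratings average between about 3.89 and 4.44. At q = 4.4 and x = 1, for example, the pooled mean is (198 + 5)/50 = 4.06, a pass.

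**Extremes.** The best possible experience (q = 5, x = 0) gives 2.5 for the weekly pair and 3.75 for the four item means, both fails, and 4.5 pooled, a pass. With q = 3.9, below the cut-off, and x = 5, the three averages are 4.45, 4.175 and 4.01, all passes. If items are judged separately, q = 3.9 still fails.

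**After reversal.** Replacing x by 5 − x turns x = 1 into 4. At q = 4.3 the weekly mean becomes 4.15 and the pooled mean 4.27, which is the intended direction. If the item is left out, the result depends on q alone.

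**The case against.** The strongest reply is that the article never says the item is averaged unreversed. Recoding a negatively worded item is often left to a scoring manual, the full protocol or the SAP, and the data management section refers to standard operating procedures. That is fair as far as it goes, and an unseen document may handle it. But the article prints the items, the anchors and the decision rule together and makes no exception. This is a rule stated wrongly, and any reversal held elsewhere would still have to be reconciled with it.

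A second reply is that, read with the Objectives, the cut-off could be meant only for motivation, satisfaction and integration, with external factors as context. On that reading nothing is inverted. This stands as a plausible intention, and for that reason the claim is limited to the rule as written. The text of the rule does not make that restriction.

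A reader might go further and infer that the acceptability verdict as a whole is inverted, or that a smooth training must fail. The documents do not support this. The diary average is one component. The overall-grade condition also applies, so a high impact rating cannot produce a positive verdict by itself. The recommendation clause can be read as sufficient alone, in which case a training that more than 80% recommend would be acceptable whatever the diary average. The text leaves open whether that clause is an alternative or a further condition. Under pooling, moreover, the item matters only near the cut-off.

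The word used is impacted, which could be neutral, but the examples of tiredness and stress make the adverse meaning clear.

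**Conclusion.** Wrong as written, of moderate severity. The diary criterion includes an item scored in the opposite direction to the other three, and it conflicts with the construct in the Objectives. The error is decisive if weekly items are judged separately or averaged together, and small if all ratings are pooled. These sizes rest on the assumed item means and, for the pooled form, on a full completer with 50 ratings.

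It would be tempting to treat this as a threat to the trial's main conclusion, because a missed criterion calls for a cautious reading of efficacy. The documents do not support that. Acceptability is a secondary outcome, secondary outcomes are analysed from an exploratory viewpoint, and the MoCA comparison, the sample size and the feasibility criteria are untouched.

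**What to change.** Remove the external-factors item from the 4/5 criterion and report it descriptively. The criterion would then rest on motivation, satisfaction and integration, as in the Objectives. If the item is to stay, reverse it as 5 minus rating before any averaging. In either case, state whether 4/5 applies to each item or to a pooled mean. It would help to say at the same time whether the recommendation clause is an alternative route to acceptability or a further condition.

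The core change costs about a sentence in the protocol and the analysis plan and uses the same diary data. It should be made before those data are analysed, since a later change to a pass/fail rule would look post hoc. Recruitment was expected to end by the close of 2025, so time is short.
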